### Surgical technique

In both groups, patients will undergo standard three-port, 25-gauge PPV by one experienced retina specialist ([name]). If epiretinal membranes are present, they will be stained and peeled. The internal limiting membrane (ILM) will be stained with brilliant blue G dye and peeled as part of the surgical procedure. The size of the ILM peel will be approximately 1 disc diameter in radius and will increase proportionally to the size of the hole with larger peels performed for larger holes. Fluid-air exchange and a complete air-gas exchange will be performed utilizing sulfur hexafluoride (SF_6_ 18%) gas. The patients in both groups will be advised to posture face down immediately following surgery.

### Interventions

Patients will be randomized 1:1 to the 3-day FDP and 7-day FDP groups. Patients will be advised to maintain the FDP for 50 minutes of each hour. They will be advised that during their 10-minute break each hour, they should avoid face-up positioning. FDP will be advised during both waking and sleeping hours. Seven days of FDP was chosen for the control group as this is the current duration advised to patients at our institution following FTMH repair. Moreover, as per the 2020 survey conducted by the ASRS evaluating the recommended duration of FDP following FTMH, this duration falls within the 5–7 day range that is most commonly utilized by retinal surgeons around the world [10]. Three days of FDP was chosen for the intervention group as in the aforementioned recent systematic review and meta-analysis on the topic, 3 days of positioning was the most frequently utilized duration when evaluating studies advising posturing positions less than 7 days [12]. Additionally, 3 days of positioning falls within the 3–4 day range which was the second most frequently recorded response in the recent ASRS survey [10]. As such comparing these two durations has the most clinical equipoise and has the potential to be the most clinically impactful.

There are no pre-specified criteria for discontinuing or modifying allocated interventions for the included trial participants. Patients will be informed regarding their allocation immediately following surgery. Patients will have an appointment with the treating team the day following surgery at which point all post-operative care including duration of positioning will be reinforced to help improve adherence. Patient adherence to their assigned positioning regimen will be self-assessed four times per day.

### Data collection methods

After enrollment, patients will undergo standardized comprehensive ophthalmic examination including slit lamp examination, VA assessment, and measurement of intraocular pressure. VA will be measured with Snellen visual acuity with the patient’s corrective lenses with pinholing to minimize the effects of refractive error. Standardized examinations along with OCT (either the Cirrus HD-OCT, Carl Zeiss Meditec, Dublin Ca or the Heidelberg Spectralis OCT, Franklin, MA depending on the availability to the research assistant) will be performed within the 2-weeks before surgery and at the following post-operative times: 1-month, and 3-months. Patients will complete the NEI-VFQ-25 and the QOLS measures at baseline, and at 3-months following surgery. Compliance will be assessed utilizing a self-administered questionnaire in which patients will be asked to rate their compliance on a scale of 1–10 upon waking (to assess the overnight period), in the morning, at midday and in the evening. Complication rates, including rates of retinal detachment, endophthalmitis and vitreous hemorrhage will be assessed by a physician at the 1-week, 1-month, and 3-month follow-up assessments.

### Data management

Data will be collected utilizing the secure online platform, Research Electronic Data Capture (REDCap) [18]. Patients will be assigned a unique study number for which their information will be linked to. In addition to the information that will be collected as part of each ophthalmic examination, the following will be collected: the patient’s age, sex, duration of symptoms, past medical history, and past ocular history.

### Sample size

The primary outcome of this investigation is to assess feasibility, as such, a power calculation to determine the sample size was not performed [15, 19, 20]. A literature review was undertaken to help inform the optimal sample size; no consensus was found with recommendations ranging from 24 to 50 described in the literature [21–23]. A previous RCT evaluating different positioning following PPV for FTMHs experienced a 10.2% attrition and thus we similarly estimate a 10% attrition rate in this investigation [24]. As such accounting for this attrition rate, utilizing a sample size of 40 patients, we will be able to estimate an 80% retention and completion rate to within a 95% confidence interval of +/-12.4% and a 33% recruitment rate to within a 95% confidence interval of +/- 14.6% [23]. We estimate based on previous rates of FTMH at our institution that there will be 3 new eligible patients each week. Previous studies at our institution have experienced a recruitment rate of 25%. Thus, we estimate that it will take approximately 53 weeks to achieve our target sample size.

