### Statistical methods and data analysis

Regarding the primary outcomes, the recruitment rate will be calculated as the number of patients randomized / the number of eligible patients screened. The retention rate will be defined as the number of patients who complete the follow-up measures at 3 months / the number of enrolled participants. Completion rates for data collection will be defined as the number of complete datasets for each of the outcome measures at 3 months / number of participants enrolled in the study. The recruitment time will be defined as the time taken in days to recruit 40 participants from the start of the enrollment period.

For the secondary outcomes, analyses will be performed on an intention-to-treat basis. Continuous variables will be expressed as means (± standard deviation) and categorical variables will be expressed as percentages. Continuous variables will be compared utilizing the student’s t-test or Mann-Whitney U test based on normality. Categorial variables will be compared utilizing the Chi-Squared Test. Fisher’s Exact Tests were performed for expected values less than five. A p-value of <0.05 will be considered statistically significant. All estimations will be reported with 95% confidence intervals. All analyses will be performed using R (version 4.3.1; R Foundation, Vienna, Austria).

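### The ±14.6% precision stated for the recruitment rate divides by 40, which is the numerator of that rate; on the defined denominator the half-width is about 8.4 points at 33% or 6.7 points at 25%

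*Protocol article*

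**What the plan says.** All the planning figures are in the Sample size section of the protocol article.

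- No power calculation was done. Literature recommendations of 24 to 50 patients are cited, and 10% attrition is expected.
- The precision statement begins "accounting for this attrition rate, utilizing a sample size of 40 patients, we will be able to estimate an 80% retention and completion rate", with a half-width of 12.4 points. It continues with "a 33% recruitment rate to within a 95% confidence interval of +/- 14.6" percent.
- For timing, the section expects that "there will be 3 new eligible patients each week" and reports: "Previous studies at our institution have experienced a recruitment rate of 25" percent. From these, "we estimate that it will take approximately 53 weeks to achieve our target sample size".

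The Statistical methods and data analysis section gives the definition: "the recruitment rate will be calculated as the number of patients randomized / the number of eligible patients screened". It also defines recruitment time as the days needed to recruit 40 participants. Retention and completion are divided by the number enrolled.

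**The concern.** A confidence interval for a proportion depends on the number of units at risk of the event. For recruitment these are the eligible patients who are screened, not those who end up randomized. The trial stops recruiting at 40 randomized patients, so 40 is fixed in advance as the numerator, and the denominator is several times larger. A half-width computed on 40 describes a different study, in which 40 eligible patients are screened and about 13 (0.33 × 40) are randomized.

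The recruitment rate is one of four named feasibility measures that make up the primary objective, and this is the only precision figure given for it. Readers planning the larger trial would take from it that the pilot can say little about accrual, when it can say appreciably more.

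**Working it through.** **Inputs.** From Sample size: 40 patients; 33% recruitment with half-width 14.6; 80% retention and completion with half-width 12.4; 25% past recruitment; 3 eligible patients a week; 53 weeks; 10% attrition. From Statistical methods and data analysis: recruitment rate = randomized / eligible screened.

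**1. Reproduce the printed figures.** Wald half-width = 1.96 × √(p(1 − p)/n).

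- Retention and completion: 1.96 × √(0.80 × 0.20/40) = 12.40 points. Matches.
- Recruitment: 1.96 × √(0.33 × 0.67/40) = 14.57 points, which rounds to 14.6. Matches.
- Solving the second for n, with half-width 0.146 and p = 0.33, gives n = 39.8, that is, 40.

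Alternatives checked for recruitment that do not give 14.6:

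| Variant | Half-width (points) |
|---|---|
| Wald, n = 36 (after 10% attrition) | 15.4 |
| Continuity-corrected, n = 40 | 15.8 |
| Wilson, 13/40 | 13.9 |
| Clopper-Pearson, 13/40 | 15.3 |

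**2. Apply the defined denominator.** Expected number of eligible patients screened = 40/p.

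| Rate | Screened | Wald | Wilson | Clopper-Pearson |
|---|---|---|---|---|
| 33% | 40/0.33 ≈ 121 | 8.4 | 8.3 | 8.7 |
| 25% | 40/0.25 = 160 | 6.7 | 6.7 | 7.0 |

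Because screening continues until 40 are randomized, inverse sampling is the stricter model. Its half-width is 1.96 × p × √((1 − p)/40), which gives 8.4 points at 33% and 6.7 points at 25%, so nothing changes.

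**3. Size of the discrepancy.** Like for like at 33%: 14.57/8.37 = 1.74.

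**4. Which rate the timeline uses.** 40/(3 × 0.25) = 53.3 weeks, the printed projection, which implies 160 eligible patients. At 33% it would be 40/(3 × 0.33) = 40.4 weeks. The recruitment window in Study timeline and status (1 December 2023 to 31 December 2024, about 57 weeks) also fits 25%.

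**5. The attrition clause.** With 36 patients (40 less 10%) the half-widths would be 1.96 × √(0.80 × 0.20/36) = 13.1 points for retention and 15.4 points for recruitment. The printed 12.4 and 14.6 both use 40.

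**The case against.** The arithmetic in steps 1 and 2 is hard to contest. The case on the other side concerns how much it matters and how far it extends, and most of that case stands.

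- **The consequences are small.** The error understates precision. The Objectives section sets its 80% cut-offs for retention and completion only, so no feasibility decision rests on the recruitment interval. The analysis section defines the rate correctly, so the planned estimate itself is sound.
- **A reader might infer that the protocol plans on two contradictory recruitment rates.** The text does not go that far. It never says that 33% is expected, only that such a rate could be estimated to a given margin. In the same sentence precision is illustrated at 80% retention, although 10% attrition implies 90%. The 33% may likewise be a reference value. It is unexplained, and the only rate used for planning is 25%.
- **A reader might infer that the figure is more than twice too wide**, from 14.6 against 6.7. That comparison changes the rate as well as the denominator. At the stated rate the factor is 1.74.
- **A reader might infer that the attrition statement is false.** The clause is ambiguous. It can mean that 40 was chosen to allow for losses, since 36/0.9 = 40. What can be said is that the printed half-widths use 40. For retention and completion that is the right number, because loss to follow-up is what retention measures.
- **A reader might infer that the choice of 40 loses its basis.** It does not. The section also rests on the cited range of 24 to 50, and the retention and completion figure is correct.

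**Conclusion.** The precision stated for the recruitment rate is wrong as written. It uses 40 as the denominator, whereas the protocol's own definition makes 40 the numerator. The half-width should be about 8.4 points at 33%, or 6.7 points at the 25% that underlies the 53-week projection, against 14.6 printed. The error is conservative, touches no feasibility cut-off and leaves the sample size unchanged. It should still be corrected, because it misstates the precision of a primary feasibility measure.

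This assumes that recruitment continues until 40 are randomized, that 40 is also the number enrolled for retention and completion, and that the rate among eligible patients is near 25% or 33%. The choice of interval method moves the corrected half-widths by no more than about 0.3 points. The unexplained 33% and the ambiguous attrition clause are points of wording, not numerical errors.

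**What to change.** Change the Sample size section as follows.

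1. Restate recruitment precision on the expected number of eligible patients screened, for example: *About 160 eligible patients will be screened to randomize 40 at an expected rate of 25%, giving a 95% confidence interval half-width of about 6.7 points.*
2. Use 25% for both precision and timing, or say why 33% is shown. If 33% is kept, the half-width is about 8.4 points on about 121 screened.
3. Keep ±12.4 points for 80% retention and completion on all 40 randomized patients.
4. Delete the attrition clause, or say that 40 was chosen to leave about 36 with follow-up and that the half-widths are computed on 40.
5. If an interval at the expected 90% retention is wanted, give Wilson for 36/40 (about 77% to 96%). The Wald half-width, 1.96 × √(0.90 × 0.10/40) = 9.3 points, gives 80.7% to 99.3%. That excludes the 80% cut-off, which the Wilson interval includes, so it would overstate what 40 patients can show.

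The cost is a text correction. The sample size, procedures and analysis do not change.

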### Participant timeline

Patients will be screened for eligibility into the trial at the time of FTMH diagnosis. Eligible patients will be identified by the trial’s supervising investigator ([name]) and will be introduced to the study at this time point. If the patient expresses interest in partaking in the study, they will be referred to one of the trial’s research assistants. This research assistant will not be involved in any aspect of the patient’s clinical care. The research assistant will review all details of the investigation with the eligible patient and will carry out the informed consent process including re-review all potential risks and benefits of enrolling in the trial with the patient. Interested eligible patients will subsequently sign an informed consent form before enrollment. During the enrollment visit, patients will undergo a complete ophthalmic examination and will have a macula OCT image taken. Additionally, patients will be provided with a vision-specific quality-of-life measure (NEI-VFQ 25) and a general quality-of-life measure (QOLS) to be completed before surgery.

Patients will undergo PPV as outlined in the *surgical technique* section and following surgery will be randomized to either the intervention (3 days of FDP) or the control (7 days of FDP) group. Patients will be informed of their allocation following surgery while in the post-anesthesia care unit. As per our institution’s current practice patterns, patients will have scheduled follow-up appointments 1 day, 1 week, 1 month and 3 months following surgery. Additionally, as per current practice patterns, patients may have additional follow-up appointments at the attending physician’s discretion. Fig 1 summarizes the participant timeline.

**Fig 1 pone.0304566.g001:**
[figure not shown]
SPIRIT figure summarizing the participant timeline. Abbreviations: PPV: pars-plana vitrectomy; OCT: optical coherence tomography; NEI-VFQ: National Eye Institute Visual Function Questionnaire’ QOLS: Quality of Life Scale.

### Recruitment

Participant recruitment will take place at the Hamilton Regional Eye Institute at the time of FTMH diagnosis. All patients will undergo OCT evaluation to ensure that they meet the study eligibility criteria. Eligible patients be informed regarding the risks, benefits, and alternatives to the surgical procedure and the different post-operative positioning durations. All patients will sign an informed consent form before enrollment into the study and before any measurement related to the study will be performed.

### Randomization and masking

Patients will be randomized 1:1 to the 3-day FDP or 7-day FDP groups utilizing permuted block randomization with blocks of 4, 6, and 8. Sequence generation will be performed in R (version 4.3.1, Vienna, Austria) by a research team member with experience generating lists for RCTs. The list will subsequently be uploaded to the online secure research platform Research Electronic Data Capture (REDCap) and allocation concealment will be maintained utilizing REDCap. Randomization will be performed immediately following completion of the surgical case and the surgeon will be immediately made aware of the patient’s allocation. At this point, the surgeon will inform the patient in the recovery room regarding their treatment allocation. Allocation concealment will be maintained utilizing REDCap. The randomization list will be made available to the remaining study team following the completion of the study.

All staff performing VA assessments and obtaining OCT images will be masked to treatment allocation. OCT grading of FTMH closure will be performed by two masked readers and disagreements will be resolved by a third masked reader. The participants themselves and the clinical teams managing their care will be unmasked.

### Study timeline and status

Ethics approval for this investigation was granted in September 2023. The research assistants for the project were subsequently trained and recruitment began on December 1^st^, 2023. Recruitment is ongoing and is expected to be complete by December 31^st^, 2024. Data collection is estimated to continue until March 2025. Data analysis and manuscript preparation is estimated to occur in the summer of 2025 at which point the manuscript will be submitted to a peer-reviewed journal. Following study completion, the results of this pilot trial will be reviewed, and a decision will be made regarding whether to proceed with a future single or multi-centered trial.

### Statistical methods and data analysis

Regarding the primary outcomes, the recruitment rate will be calculated as the number of patients randomized / the number of eligible patients screened. The retention rate will be defined as the number of patients who complete the follow-up measures at 3 months / the number of enrolled participants. Completion rates for data collection will be defined as the number of complete datasets for each of the outcome measures at 3 months / number of participants enrolled in the study. The recruitment time will be defined as the time taken in days to recruit 40 participants from the start of the enrollment period.

For the secondary outcomes, analyses will be performed on an intention-to-treat basis. Continuous variables will be expressed as means (± standard deviation) and categorical variables will be expressed as percentages. Continuous variables will be compared utilizing the student’s t-test or Mann-Whitney U test based on normality. Categorial variables will be compared utilizing the Chi-Squared Test. Fisher’s Exact Tests were performed for expected values less than five. A p-value of <0.05 will be considered statistically significant. All estimations will be reported with 95% confidence intervals. All analyses will be performed using R (version 4.3.1; R Foundation, Vienna, Austria).

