### Objectives

Our primary objective will be focused on assessing feasibility. Feasibility will be assessed by measuring the recruitment rate, retention rate, and completion rate at 3 months following surgical repair as well as the recruitment time.

Our secondary outcomes will include a) macular hole closure rate at 3 months following surgery; two independent readers, masked to treatment allocation, will independently grade the outcome in each instance as closed, or open. Outcomes classified as open will be further divided into open and flat (without a cuff of subretinal fluid), or open and elevated (with a cuff of subretinal fluid). b) best-recorded visual acuity at 3 months post-surgery, c) compliance with FDP as assessed utilizing self-administered questionnaires four times per day during the duration of FDP, d) patient self-administered vision-specific validated quality of life measure, the 25-item National Eye Institute Visual Function Questionnaire (NEI VFQ-25) and a validated quality of life measure, the Quality of Life Scale (QOLS), and e) complication rates (endophthalmitis, retinal detachment, vitreous hemorrhage) as assessed by a masked physician.

The interpretation of findings will be: a) the full-scale trial is feasible with no changes to the protocol; b) the full-scale trial is feasible with small changes to the protocol; c) the full-scale trial is infeasible. The study will be considered feasible if the retention and completion rates are > 80% of randomized patients. The study will be considered feasible with small changes if either the retention or completion rate is <80% of randomized patients and the study will be considered infeasible if the completion and retention rates are <80% of randomized patients.

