**Methods: Data collection, management, and analysis**			
Data collection methods	18a	Plans for assessment and collection of outcome, baseline, and other trial data, including any related processes to promote data quality (eg, duplicate measurements, training of assessors) and a description of study instruments (eg, questionnaires, laboratory tests) along with their reliability and validity, if known. Reference to where data collection forms can be found, if not in the protocol	15
	18b	Plans to promote participant retention and complete follow-up, including list of any outcome data to be collected for participants who discontinue or deviate from intervention protocols	15
Data management	19	Plans for data entry, coding, security, and storage, including any related processes to promote data quality (eg, double data entry; range checks for data values). Reference to where details of data management procedures can be found, if not in the protocol	15
Statistical methods	20a	Statistical methods for analysing primary and secondary outcomes. Reference to where other details of the statistical analysis plan can be found, if not in the protocol	18, 19
	20b	Methods for any additional analyses (eg, subgroup and adjusted analyses)	N/A
	20c	Definition of analysis population relating to protocol non-adherence (eg, as randomised analysis), and any statistical methods to handle missing data (eg, multiple imputation)	18, 19

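### Visual acuity, NEI VFQ-25 and QOLS are to be compared without baseline adjustment, by a test chosen on normality, although each is measured before surgery: valid, but imprecise, and it leaves the estimand open

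*Protocol article*

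**What the plan says.** The Statistical methods and data analysis section of the protocol article sets one rule for every continuous secondary outcome: "Continuous variables will be compared utilizing the student’s t-test or Mann-Whitney U test based on normality". The same paragraph promises means with standard deviations and 95% confidence intervals for all estimates. No covariate is named. Table 1, the SPIRIT checklist, marks item 20b as N/A; that item reads "Methods for any additional analyses (eg, subgroup and adjusted analyses".

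Three of the outcomes under this rule have a pre-operative value:

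- **Quality of life:** "Patients will complete the NEI-VFQ-25 and the QOLS measures at baseline, and at 3-months following surgery" (Data collection methods). Participant timeline confirms that both questionnaires are to be completed before surgery.
- **Visual acuity:** "VA will be measured with Snellen visual acuity with the patient’s corrective lenses". The standardized examination that contains it "will be performed within the 2-weeks before surgery and at the following post-operative times: 1-month, and 3-months" (Data collection methods). Objectives defines the outcome as "best-recorded visual acuity at 3 months post-surgery".

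A fourth continuous measure, the self-rated compliance score on a 1 to 10 scale, is collected only while the patient is positioning, so it has no baseline.

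**The concern.** In a trial this small, a patient's pre-operative vision or questionnaire score may explain a fair share of the variation at 3 months. An analysis that leaves it out puts that variation into the standard error. Randomization uses permuted blocks with no stratification factor named, so the design does not balance baseline vision either.

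The second part concerns what is being estimated. A t-test goes with a difference in means. A Mann-Whitney test compares ranks and does not by itself give a mean difference or an interval for one. If a normality check on roughly 20 values per arm picks the test, the data decide which quantity is reported, and VA, NEI VFQ-25 and QOLS could end up on different footings. That sits badly with a promise of means and 95% intervals throughout.

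At stake are the width and the meaning of the intervals that the pilot will publish for these outcomes. The Discussion calls postoperative VA one of the two outcomes that experts ranked highest.

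**Working it through.** **Plan's own figure.** There is none for the continuous outcomes. The half-widths in Sample size concern proportions. They reproduce with n = 40: 1.96 × √(0.80 × 0.20/40) = 12.4% and 1.96 × √(0.33 × 0.67/40) = 14.6%. The same normal quantile is used below.

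**Inputs**

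- Total size: "utilizing a sample size of 40 patients" (Sample size), allocated 1:1.
- Attrition: "we similarly estimate a 10% attrition rate in this investigation" (Sample size), so 40 × 0.9 = 36 analysed, 18 per arm.
- Correlation r between baseline and 3-month value: not in the documents. Assumed range 0.3 to 0.7.
- Significance level 0.05, taken as two-sided because the article does not say.

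**Precision.** In units of the outcome SD, the unadjusted half-width is 1.96 × √(2/18) = 0.65. ANCOVA on the baseline value multiplies the variance by 1 − r² and the half-width by √(1 − r²).

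| Assumed r | Variance factor | SD factor | 95% half-width (SD) |
|---|---|---|---|
| unadjusted | 1 | 1 | 0.65 |
| 0.3 | 0.91 | 0.95 | 0.62 |
| 0.5 | 0.75 | 0.87 | 0.57 |
| 0.7 | 0.51 | 0.71 | 0.47 |

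These are large-sample factors. With 36 patients and a normal covariate, estimating the slope costs on average a factor (N − 3)/(N − 4) = 33/32 = 1.03 in variance. At r = 0.3 the net saving is therefore nearer 6% than 9% (0.91 × 1.03 = 0.94).

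**If change scores were meant.** The SD of a change is √(2(1 − r)) times the outcome SD: 1.18, 1.00 and 0.77 for r = 0.3, 0.5 and 0.7. Each exceeds the ANCOVA factor in the table, so the conclusion does not depend on which was intended.

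**Simulation.** 4,000 trials per setting, 18 per arm. The two-stage rule used a t-test if both arms passed a Shapiro-Wilk test at 0.05, and otherwise Mann-Whitney. The skewed outcome was a standardized lognormal (log-scale SD 0.8), with baseline left normal and r set before exponentiation.

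| Setting | r = 0.3 | r = 0.5 | r = 0.7 |
|---|---|---|---|
| Type I error, two-stage, normal | 0.045 | 0.047 | 0.056 |
| Type I error, two-stage, skewed | 0.050 | 0.048 | 0.050 |
| Power at 0.8 SD, normal: two-stage | 0.645 | 0.634 | 0.643 |
| Power at 0.8 SD, normal: ANCOVA | 0.679 | 0.748 | 0.897 |
| Power at 0.8 SD, skewed: two-stage | 0.922 | 0.932 | 0.922 |
| Power at 0.8 SD, skewed: t-test | 0.726 | 0.706 | 0.719 |
| Power at 0.8 SD, skewed: untransformed ANCOVA | 0.737 | 0.765 | 0.854 |

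With normal data ANCOVA is ahead at every r. With marked skew it still beats the t-test, but it loses to the two-stage rule, which then mostly selects the rank test.

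**The case against.** The strongest reply is that nothing here is invalid and little depends on it. These are secondary outcomes in a pilot with no power calculation. The rule in Objectives rests on retention and completion alone, and the article concedes that the clinical question will not be answered. That stands, and it limits the weight of the point.

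It is also fair that a condensed article may leave the VA scale, and the choice between final value and change, to a fuller document. Those gaps are not raised as faults. The choice of test is different: the article makes it, and the checklist rules adjusted analyses out.

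The size of the gain is assumed throughout. At the low end of the range the interval barely moves.

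Four stronger readings are tempting, and the documents or the check do not support them:

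- *A reader might infer that the unadjusted SD is wrong for planning the main trial.* No section says that the pilot SD will size it. The marginal SD is right for an unadjusted main analysis and conservative for an adjusted one, and the residual SD can be derived later from the same data.
- *A reader might infer that chance baseline imbalance biases the comparison.* Under randomization the unadjusted estimate is unbiased, and its interval already allows for such imbalance. The loss is one of precision.
- *A reader might infer that the normality check inflates false positives.* The simulated type I error stayed between 0.045 and 0.056.
- *A reader might infer that ANCOVA is better in every case.* Under marked skew the planned route had more power than untransformed ANCOVA.

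**Conclusion.** The point holds as a modest, low-cost improvement. The article commits to an unadjusted comparison of three outcomes whose baselines are already collected, and it lets a normality check decide between means and ranks while promising means and intervals.

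The loss is between 9% and 49% of variance if r lies between 0.3 and 0.7. It would be near zero if baseline hardly predicts the 3-month value, which is possible after surgery meant to change vision. The half-widths assume 18 per arm, a linear relation and roughly normal residuals. The open estimand does not depend on r. No conclusion about feasibility changes.

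**What to change.** Replace the sentence on continuous variables, for these three outcomes, with the following:

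- Analyse 3-month VA (Snellen converted to logMAR), NEI VFQ-25 and QOLS by ANCOVA, with arm and the outcome's own baseline as terms.
- Report the adjusted mean difference with its 95% interval, the raw SD and the baseline to 3-month correlation.
- Drop the normality-based choice. Name one robust interval method in advance, for example a bootstrap interval, and use it whatever the residuals look like, so that one data-driven step is not exchanged for another.
- Leave the compliance rating unadjusted, since it has no baseline.
- Bring the entry for SPIRIT item 20b into line.

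Reporting both the raw SD and r lets a later team plan either kind of analysis. For an illustrative 0.5 SD difference at 80% power, n per arm = 2 × (1.96 + 0.84)² × (1 − r²)/0.5². That gives 63 unadjusted, and 58, 48 or 33 for r = 0.3, 0.5 or 0.7.

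The cost is a change of wording, one degree of freedom per model, and possibly some power against a rank test if an outcome is markedly skewed. No new data or visits are needed. The logMAR scale and the bootstrap interval were not part of the simulation, so how far they offset the skew problem is untested here.
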